### Study procedures

Study procedures are summarized in Fig 2. Pregnant women between 28 + 0 and 37 + 0 weeks of gestation who participate in the antenatal preparation course sponsored by the Fondazione Policlinico Agostino Gemelli IRCCS will be informed about this study. The antenatal preparation course is held monthly, and it encompass nearly 60 women per course. Women who express interest will be scheduled for an in-person appointment with a research midwife, during which they will undergo eligibility screening. Those meeting the inclusion criteria and providing written informed consent will be randomized into one of two groups:

Midwife-led TPUS-guided pushing training group.Midwife-led pushing training only group (control).

**Fig 2 pone.0352315.g002:**
[figure not shown]
PURSUE study design.

### Pushing Training Program

The pushing training program consists of a two-hour in-person session, structured as follows:

30 minutes of theoretical instruction, covering the physiological mechanisms of labour, the role of the LAM during pushing, and optimal pushing techniques.30 minutes of practical exercises, during which women will be guided through breathing techniques, pushing strategies, and perineal relaxation.

Women randomized to the TPUS-guided pushing training group receive additional TPUS evaluations during practical exercises, performed by a midwife trained in ultrasound imaging. The intervention is delivered by two midwives and three assistant midwife researchers. To ensure consistency and reduce inter-operator variability, the same midwife-assistant pair delivers the training to each allocated group throughout the study period. All midwives involved in the training received a minimum of one week of training on TPUS by a gynecologist with more than three years of experience in pelvic floor ultrasound. During training, all the midwives learned to perform TPUS in the midsagittal view with a Samsung HM70 EVO (Fig 3). Midwives learned to visualize pubic symphysis, fetal head, rectum and puborectalis muscle. To assess whether the LAM relax during the TPUS-guided pushing training, midwives measure the APD of the levator hiatus, from the posteroinferior border of the pubic symphysis to the anterior border of the puborectalis muscle (the main portion of the LAM), at rest and on maximum pushing manoeuvre, according to a previously described technique (Fig 3). During visual feedback, each woman watches the ultrasound screen to visualize the movement of the puborectalis muscle during pushing.

**Fig 3 pone.0352315.g003:**
[figure not shown]
Transperineal ultrasound images illustrating measurement of anteroposterior diameter of levator hiatus, running from inferior border of pubic symphysis to anterior border of puborectalis muscle.

Midwives who delivered the educational intervention were different from those who provided intrapartum care during delivery, thereby minimising the risk of performance bias arising from knowledge of treatment allocation during labour. At the time of delivery, randomized women are instructed to push freely, following the techniques and guidance they previously received during the training sessions.

### Data collections

Data will be collected at multiple time points throughout the study to ensure comprehensive evaluation of the interventions’ effectiveness and safety (Fig 1). At enrolment, baseline demographic and obstetric information, including maternal age, parity, medical history, and pregnancy details, will be recorded. During the intervention period, attendance and engagement with both the online educational video and in-person sessions will be tracked. For participants in the TPUS-guided arm, detailed observations and measurements captured through TPUS will be documented during practical exercises to assess technique and muscle engagement.

Delivery outcomes will be extracted from medical records, including mode of birth (vaginal or caesarean section), duration of second stage of labour, incidence of any degree perineal tears, and any complications. Following childbirth, women’s satisfaction with the delivery experience will be evaluated using validated questionnaires. Women will be contacted at 6, 12 and 16 weeks post-partum. At each time point, urinary incontinence will be assessed using the ICIQ-SF questionnaire. At the 16 weeks follow-up, women will additionally be asked whether they have attended pelvic floor rehabilitation sessions since delivery. Collected data will be handled using a secure, de-identified database, with regular checks to ensure data integrity and adherence to ethical guidelines. Pseudonymized datasets will be stored on Zenodo (https://zenodo.org/), a secure open-access platform compliant with EU data protection regulations and FAIR principles.

### Randomization, blinding and treatment allocation

Once eligibility is confirmed and informed consent is obtained, participants will be randomised (1:1) into one of two study arms: using a computer-generated random sequence (“randomizeR” package in R**).** Assignment to study groups will be managed through sealed, opaque and sequentially numbered envelopes accessible only to the research midwife, thereby maintaining allocation concealment until the moment of assignment.

Given the nature of the interventions, this study is designed as an open-label trial; both the participants and the researchers will be aware of the group assignments. While full blinding is not feasible due to the involvement of TPUS in one arm, outcome assessors will be blinded to group allocation when evaluating outcomes and analysing data. This approach aims to reduce assessment bias and ensure that the treatment allocation does not influence the collection and interpretation of results.

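### The assessor-blinding claim cannot hold for the self-reported CEQ-2 and ICIQ-SF, and using different midwives in labour reduces performance bias without masking the ward

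*Protocol article*

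**What the plan says.** All references are to the protocol article.

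- *Randomization, blinding and treatment allocation* calls the trial open-label and says that "both the participants and the researchers will be aware of the group assignments". It concedes that full blinding cannot be achieved. It then says that "outcome assessors will be blinded to group allocation when evaluating outcomes and analysing data", with the aim of reducing assessment bias and to "ensure that the treatment allocation does not influence the collection and interpretation of results". No outcome is excepted.
- *Objectives* and *Data collections* make maternal satisfaction a CEQ-2 score from 0 to 100. They also say that "urinary incontinence will be assessed using the ICIQ-SF questionnaire", at 6, 12 and 16 weeks after birth.
- *Pushing Training Program* (the text after Fig 3) states: "Midwives who delivered the educational intervention were different from those who provided intrapartum care during delivery". It draws the consequence "thereby minimising the risk of performance bias arising from knowledge of treatment allocation during labour". In labour, "randomized women are instructed to push freely, following the techniques and guidance they previously received during the training sessions".
- *Setting* says that attending midwives coach pushing verbally and that care in labour is the same in both arms.
- *Statistical analysis plan* starts the primary interval at the first coordinated push, whether spontaneous or prompted by midwifery coaching. Times are entered in the partogram during labour, and a blinded researcher extracts them later. All secondary analyses are labelled exploratory.

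**The concern.** There are two separate mechanisms, and they affect different outcomes.

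The first is self-report. For CEQ-2 and ICIQ-SF, the person who evaluates the outcome is the participant. The paragraph that says assessors are blinded also says participants know their arm. For these two outcomes the design lacks the property the text claims. CEQ-2 is the more exposed: control women know they did not have the ultrasound session, and the *Expected results* section anticipates greater satisfaction and sense of control with biofeedback. Read with the blinding statement, a difference in CEQ-2 could be given more weight than an unblinded self-report deserves.

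The second is knowledge of the arm on the labour ward. Different staff are not masked staff. A ward midwife who learns the arm can coach, time or record differently, and this happens before the blinded researcher sees the record. Blinded extraction protects against biased extraction. It cannot remove a bias already in the partogram. This mechanism bears on the primary endpoint and other intrapartum outcomes, and has little to do with ICIQ-SF at 6 to 16 weeks.

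**Working it through.** **Who rates each outcome, and is that person blinded?**

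| Outcome | Who produces the value | Blinded when produced? | Later blinded step |
|---|---|---|---|
| CEQ-2 | The woman | No; the article says she knows her arm | Analysis |
| ICIQ-SF at 6, 12, 16 weeks | The woman | No; same reason | Analysis |
| Active pushing time (primary) | Recorded during labour in the partogram | Not stated; training staff are different people | Extraction and analysis |
| Mode of birth, tears, complications | Ward record | Not stated | Evaluation and analysis, under the general statement |

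For the first two rows the blanket claim contradicts the sentence before it. For the last two, blinding is supported only from extraction or later evaluation onward.

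**The plan's own figures.** No figure is in dispute, but the standard error below uses the planned inputs, so I checked them first.

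- Pooled SD: √((63² + 42²)/2) = √2866.5 = 53.5 minutes, as stated.
- Effect size: 20/53.5 = 0.374, as stated (0.37).
- Sample size, two-sided 5%, 80% power: 113 per arm by normal approximation; 113.3, rounded up to 114, by t-test. The stated 114 reproduces.
- Enrolment: 228/0.85 = 268.2, matching the stated 268.

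**Illustration 1: primary endpoint.** The unadjusted standard error of the arm difference is 53.5 × √(2/114) = 7.09 minutes. With no true effect and a differential shift b from staff behaviour or recording, the chance of a significant result is P(|Z + b/7.09| > 1.96).

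| Assumed shift b (minutes) | b/SE | Two-sided error (nominal 5%) |
|---|---|---|
| 2 | 0.28 | 6% |
| 3 | 0.42 | 7% |
| 5 | 0.71 | 11% |
| 7 | 0.99 | 17% |
| 10 | 1.41 | 29% |

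**Illustration 2: a continuous self-report such as CEQ-2.** With a pure reporting shift of d standard deviations, b/SE becomes d × √(n/2).

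| Assumed shift d (SD) | Error, 114 per arm | Error, 134 per arm |
|---|---|---|
| 0.1 | 12% | 13% |
| 0.2 | 33% | 37% |
| 0.3 | 62% | 69% |

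Every shift in both tables is an assumption. The documents give no figure for either bias, so the tables show sensitivity, not an expected size.

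**The case against.** The strongest defence is that the article hides nothing. It declares the trial open-label, concedes that full blinding cannot be achieved, and says the approach aims to reduce assessment bias. Every secondary analysis is exploratory, so no confirmatory claim rests on CEQ-2 or ICIQ-SF. Blinded analysis can apply to both. All of this stands and limits the weight of the point, but it does not make the unqualified assessor statement true for outcomes that the women rate themselves.

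A reader might infer something stronger: that nothing keeps the arm from the labour ward, or that the stated protection does not exist. The documents do not support that.

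- Staff separation, and envelopes open only to the research midwife, are partial safeguards. Blinded extraction is specified for both time intervals.
- A woman who follows her training does not thereby reveal her arm. Both arms are taught breathing, pushing strategies and perineal relaxation in the same programme; the intervention arm adds ultrasound evaluation and visual feedback. Disclosure would have to be verbal or through records.
- The article does not say whether women are asked to withhold their arm or whether it appears in the labour record. A condensed article may leave such procedures to the full protocol, so this silence is not a fault in the plan.

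It is also fair to say that the shift calculations could be attached to any open-label trial. They show that modest shifts would matter at this sample size, not that such shifts occur. What survives on the ward side is narrower: separating staff does not mask them, so the inference that performance bias is minimised goes further than the measure.

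**Conclusion.** The point holds in two parts.

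1. The assessor-blinding statement is wrong for the rating of CEQ-2 and ICIQ-SF. This follows from the article's own text and needs no assumption beyond the women answering the questionnaires themselves.
2. Staff separation lowers the risk of performance bias but does not establish that it is minimised. Ward midwives coach pushing, coaching can precede the push that starts the primary clock, and the time is recorded during labour before blinded extraction. Whether ward staff in fact learn the arm is unknown from the documents.

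The size of any bias is likewise unknown. Under assumed differential shifts of 3 to 7 minutes, the error rate on the primary endpoint would rise from 5% to between 7% and 17%. The sample size is unaffected. Because the questionnaires are exploratory and the open-label design is openly stated, this is a minor to moderate point, mainly about what may be concluded from the results.

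**What to change.** 1. In *Randomization, blinding and treatment allocation*, limit the blinding claim to extraction of outcomes from records and to statistical analysis. State that CEQ-2 and ICIQ-SF are unblinded self-reports and will be interpreted as such.
2. In *Pushing Training Program*, say that using different midwives for training and labour reduces, rather than minimises, performance bias.
3. If not already done, ask women at training not to tell ward staff their arm, and keep the arm out of the labour record and partogram.

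Optionally, add one item to the birth form on whether the attending midwife knew the arm, reported by arm. This would show how much disclosure occurred, but the correction does not depend on it.

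The first two changes are wording only and can be made at any time. The third is one line of participant instruction and a check on record handling; it can help only births still to come, with enrolment planned to 31/07/2026. None of these changes alters the endpoint, the sample size or care. The downside is that some disclosure will still occur.

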### Sample size

The sample size was calculated to detect a mean reduction of 20 minutes in the duration of the active second stage of labour in the experimental group compared with the control group. Twenty minutes was pre-specified as the minimal clinically important difference for the duration of the active pushing phase, rather than as the anticipated magnitude of the treatment effect. Its clinical relevance is anchored to preliminary data showing that nulliparous women with LAM co-activation experience a longer second stage than those without co-activation (83 ± 63 vs. 63 ± 42 minutes, respectively). The pooled standard deviation is 53.5 minutes, yielding a standardised effect size (Cohen’s d) of 0.37, corresponding to a small-to-medium effect consistent with published trials of intrapartum ultrasound-based biofeedback interventions which were delivered intrapartum rather than antenatally. Using a two-sided independent-samples test with α = 0.05 and 80% power, the required sample size is 114 participants per arm (228 total). To account for an anticipated 15% attrition rate, encompassing study dropout, caesarean delivery before or during labour, and operative vaginal delivery precluding assessment of the primary endpoint, the final enrolment target has been set at 268 participants (134 per arm). We acknowledge that the hypothesised effect size assumes a biologically plausible benefit across the entire intervention group. Because preliminary data suggest that approximately 25% of nulliparous women exhibit LAM co-activation, the treatment effect may be attenuated in the overall population if benefit is concentrated in this subgroup. A pre-specified within-arm analysis by co-activation status at training is planned to explore this hypothesis (see Statistical Analysis Plan).

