**Methods and analysis:**

PURSUE is a single-centre, open-label, parallel-group RCT at Fondazione Policlinico A. Gemelli, Rome reported according to the SPIRIT 2013 and CONSORT 2010 guidelines. Nulliparous women between 28 + 0 and 37 + 0 weeks of gestation will be randomised 1:1 to midwife-led pushing training without ultrasound biofeedback or a midwife-led session combining theoretical instruction with real-time TPUS-guided pushing training. The primary endpoint is duration of the active second-stage of labour (minutes). Secondary outcomes include levator ani co-activation amplitude, spontaneous vaginal birth, perineal trauma, postpartum haemorrhage ≥ 500 mL, urinary/faecal incontinence at 6, 12 and 16 weeks postpartum and childbirth experience (CEQ-2). A sample of 228 (114 per arm) provides 80% power to detect a clinically meaningful reduction of 20 minutes(Cohen’s d = 0.37; α = 0.05, two sided). Allowing for 15% attrition, 268 women will be enrolled. The primary analyses uses multivariate linear regression adjusting for pre-specified covariates; secondary analyses are exploratory.

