#### Setting.

This single-center study will be conducted at Fondazione Policlinico Universitario Agostino Gemelli IRCCS Rome, an academic private tertiary-level hospital located in central Italy, with over 4,000 births per year. Childbirth care is characterised by continuous one-to-one intrapartum support provided by registered midwives under the supervision of senior midwives and obstetricians. Second-stage management follows physiological principles. In nulliparous women with epidural analgesia, delayed pushing is practised until the urge to push is felt or the fetal head reaches the pelvic floor; active pushing is then maternal-led, with verbal coaching by attending midwives. Practitioners do not routinely use ultrasound during the pushing stage to assess fetal station or perineal status. Intrapartum care is identical for both study arms; only the antenatal training component differs. In 2025 the hospital recorded an epidural analgesia rate of 72%, a primary cesarean section rate of 19%, and an operative vaginal delivery rate of approximately 11%, performed by vacuum extraction (Kiwi Cup).

Although a dedicated pelvic floor outpatient unit is available, no standardized postpartum pelvic floor rehabilitation protocol is in place. Rehabilitation sessions are therefore not scheduled as part of routine care, and attendance at external pelvic floor rehabilitation is not systematically recorded. All women are nonetheless advised at discharge of the importance of pelvic floor evaluation in the postpartum period. Attendance at pelvic floor rehabilitation will be recorded at the16 weeks follow-up contact. Should the rate of rehabilitation uptake exceed 10% in either arm, it will be included as a covariate in exploratory sensitivity analyses for pelvic-floor related outcomes.

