The primary endpoint will be analysed using multivariable linear regression, with treatment arm as the main predictor. The model will be adjusted for pre-specified baseline covariates only, that is, variables measured before randomisation: maternal age, body mass index at enrolment, gestational age at randomisation, maternal height, and sonographic estimated fetal weight at the last available third-trimester scan. Consistent with ICH E9, no post-randomisation variable is included in the confirmatory model, since conditioning on variables measured after allocation may invalidate the randomisation-based causal interpretation of the treatment effect. This applies in particular to fetal head position at full cervical dilatation, epidural analgesia and gestational age at delivery, which are potential intermediate variables on the causal pathway between the intervention and the primary endpoint. Their distribution across arms will be reported descriptively, and epidural analgesia and fetal head position will be examined as potential effect modifiers through interaction terms, as exploratory analyses. The primary result will be reported as an adjusted mean difference with 95% confidence interval; the p-value will be provided as secondary inferential information. If the residuals of the linear model indicate substantial departure from normality, a bootstrap confidence interval will be computed. Women who do not reach the active second stage (e.g., caesarean delivery before full dilatation) will not contribute to the primary analysis but will be retained in the ITT population for all secondary outcomes. For clarity, the primary estimand may therefore be summarised as the difference in adjusted mean duration of the active pushing phase between arms among randomised nulliparous women reaching the active second stage, with operative vaginal delivery and second-stage caesarean section handled under a treatment-policy strategy as delivery events at the observed time. The number of women contributing to each analysis, with the corresponding denominators and reasons for non-contribution, will be reported by arm in the CONSORT flow diagram, and the baseline characteristics of women not reaching the active second stage will be compared between arms using standardised mean differences. Sensitivity analyses will include multiple imputation under the missing-at-random assumption and inverse probability weighting to assess the robustness of the primary estimate to differential attrition, applied to observations that are missing rather than undefined, such as incomplete partogram times or non-returned questionnaires; where an imbalance is observed in the proportion of women reaching the active second stage, inverse probability of selection weights will be applied accordingly. Time to spontaneous vaginal birth from the onset of active pushing will additionally be described using cumulative incidence functions, with operative vaginal delivery and second-stage caesarean section treated as competing events rather than as censored observations, and compared between arms using Gray's test. This analysis is supportive and exploratory.

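### The 15% attrition allowance in the Sample size section does not match the primary estimand or the hospital's 19% caesarean rate, so 228 analysable women and 80% power are not supported as stated

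*Protocol article*

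**What the plan says.** The Sample size section targets a 20-minute difference: "The sample size was calculated to detect a mean reduction of 20 minutes in the duration of the active second stage of labour". It takes the variability from preliminary data ("83 ± 63 vs. 63 ± 42 minutes, respectively") and states: "The pooled standard deviation is 53.5 minutes, yielding a standardised effect size (Cohen’s d) of 0.37". "Using a two-sided independent-samples test with α = 0.05 and 80% power", it arrives at 114 women per arm, 228 in all. It then raises this to 268 on the basis of this allowance: "anticipated 15% attrition rate, encompassing study dropout, caesarean delivery before or during labour, and operative vaginal delivery precluding assessment of the primary endpoint". In the abstract the result is repeated: "Allowing for 15% attrition, 268 women will be enrolled".

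Two other sections bear on that allowance.

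- The Setting section gives the hospital's 2025 figures: "a primary cesarean section rate of 19%, and an operative vaginal delivery rate of approximately 11" per cent.
- The Statistical analysis plan section leaves out of the primary analysis only women who never get to the active second stage. Its estimand has "operative vaginal delivery and second-stage caesarean section handled under a treatment-policy strategy as delivery events at the observed time". The endpoint runs from the first expulsive effort to birth, so a birth by vacuum or second-stage caesarean still has a duration.

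**The concern.** The allowance fails against the rest of the document in two ways.

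First, its list of losses is not the list that the primary analysis uses. It treats caesarean at any point in labour as a loss, along with operative vaginal births that prevent assessment. The estimand keeps second-stage caesareans and operative vaginal births at their observed time. The enrolment target was therefore set for a different group of women from the one to be analysed.

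Second, the 15% is not set against the rates that the same document reports. On its own list, the hospital's caesarean rate already exceeds it, with nothing left for dropout.

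At stake is whether the stated 228 analysable women and 80% power can be relied on. The two faults pull in opposite directions: using the hospital rate raises the expected loss, while following the estimand lowers it. The net effect therefore has to be calculated.

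**Working it through.** **Inputs.** Difference 20 minutes, SDs 63 and 42, two-sided α 0.05, power 80%, 15% loss and 268 enrolled (Sample size). Caesarean 19%, operative vaginal delivery about 11% (Setting). Not given in the document: the share of caesareans that precede active pushing, and a separate dropout rate.

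**The plan's own figures.** Pooled SD = √((63² + 42²)/2) = 53.5, and d = 20/53.5 = 0.37. Normal approximation: n per arm = 2 × (1.960 + 0.842)² × 53.5²/20², which rounds up to 113. The t-test gives 113.3, hence 114 per arm, with power 80.2%. Inflation: 228/0.85 = 268.2, and 268 × 0.85 = 227.8. The stated numbers reproduce, so the problem lies in the 15% and not in the arithmetic that follows from it.

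**Power for other losses.** Analysable N = 268 × (1 − loss). Power is that of a two-sample t-test with N/2 per arm, difference 20 and SD 53.5. The normal approximation runs 0.3 to 0.5 points higher.

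**A. The Sample size list with the Setting rate.** All caesareans lost, no dropout: 268 × 0.81 = 217.1 women, power 78.3%. Check by normal approximation: 20/(53.5 × √(2/108.5)) = 2.75, and Φ(2.75 − 1.96) = 78.6%. This counts no operative vaginal birth and no dropout as lost, so on this list at the hospital rate it is the smallest possible loss.

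**B. The analysis rule.** Only women with a caesarean before active pushing, and dropouts, are lost. Loss = 1 − (1 − 0.19 × share) × (1 − dropout). Shares and dropout rates are assumptions. Cells give analysable women and power.

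| Share of the 19% before pushing | Dropout 0% | Dropout 5% | Dropout 10% |
|---|---|---|---|
| 50% | 242.5; 82.6% | 230.4; 80.7% | 218.3; 78.5% |
| 75% | 229.8; 80.6% | 218.3; 78.5% | 206.8; 76.3% |
| 100% | 217.1; 78.3% | 206.2; 76.2% | 195.4; 73.9% |

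**When 15% is enough under B.** The caesarean rate before pushing must not exceed 1 − 0.85/(1 − dropout). That is 15.0%, 10.5% or 5.6% at dropout of 0%, 5% or 10%, or 79%, 55% or 29% of the 19%. The document does not say whether any of these conditions is met.

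**The case against.** A reader might infer that 268 women cannot deliver 228 or 80% power. The documents do not support that. Under the analysis rule three of the nine cells above reach both, and the inputs that decide between cells are not given. The 19% describes the whole hospital. The trial takes only nulliparous women and excludes contraindications to vaginal birth, so its rate could lie on either side. The SD also matters. If 25% of women co-activate, as the Sample size section suggests, its own figures give √(0.25 × 63² + 0.75 × 42² + 0.25 × 0.75 × 20²) = 48.9. About 190 women would then give 80% power, and 268 would tolerate roughly 29% loss. Covariate adjustment could help too: if covariates explained 5% of the variance (assumption), 217 women would give 80.2%.

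A reader might also add 19% and 11% to claim a 30% loss (187.6 women, 72.1% power). That overreads the text, which counts only operative vaginal births that prevent assessment. With an endpoint that ends at birth, few need do so.

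Nor is the analysis set open to choice once data are seen. The Statistical analysis plan section fixes it and requires denominators and reasons for non-contribution by arm. The Sample size list is a planning allowance and does not define a rival analysis set.

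These points limit the consequence but leave the inconsistency. The qualifier on operative births does not clearly extend to caesareans. Even if it did, the 15% would still not be reconciled with the 19%, and operative vaginal delivery would still be listed as a source of loss that the estimand does not recognise.

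**Conclusion.** The point holds as an inconsistency that should be fixed. The 15% allowance counts events that the primary analysis retains, and it is below the caesarean rate quoted in the same document. On the Sample size list, with the hospital rate taken as the trial's, at least 19% are lost before dropout. That leaves about 217 women and about 78% power, which is 11 women and about two points short of the stated figures. Under the estimand the outcome runs from about 242 women and 83% power to about 195 and 74%, for the assumed 50% to 100% of caesareans before pushing and 0% to 10% dropout. All of this is at SD 53.5 with an unadjusted test. A shortfall is possible but not certain, and the validity of the primary analysis is not in question.

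**What to change.** Keep the estimand in the Statistical analysis plan section. In the Sample size section:

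- delete operative vaginal delivery and second-stage caesarean from the attrition list;
- state separately the expected proportion of women not reaching active pushing, justified against the 19% in the Setting section, and the expected dropout rate;
- restate the expected analysable number and the resulting power as a range, with the assumptions named.

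Carry the same statement into the Methods and analysis paragraph of the abstract.

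This is a change of wording only and no extra enrolment is required. Its cost is that the stated power may become slightly less favourable. If the sponsor prefers to hold 228 analysable women, enrolment would be about 282 at a total loss of 19% (228/0.81 = 281.5) or 304 at 25% (228/0.75).
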